### Data management

All data will be handled confidentially and anonymized in compliance with the Dutch Personal Data Protection Act (“Wet Bescherming Persoonsgegevens”). Questionnaires are collected digitally and the patient study data will be stored coded using data management software (Research Manager version 5.30.0.6, Cloud9 Software, Deventer, The Netherlands). Each patient receives an anonymized study number that is used for all documentation, study reports and publications. The key of this study number will be handled by an independent researcher. All data will be stored during the study period, and when the study is finished, the research files are stored for 15 years in the Máxima Medical Center research archive. The Medical Research Ethics Committee deemed the study as a “low-risk” study. Therefore, no Data Monitoring Committee was recommended at the time of ethical approval. The Medical Research Ethics Committee will be informed yearly on the inclusion rate, adverse events and study results.

### Statistical analysis

The primary analysis will be performed according to intention-to-treat principles following the original group allocation regardless of the intervention that they actually received. Missing data will be accounted for by a multiple imputation technique. A secondary per-protocol analysis will be performed, including only those patients who completed the treatment originally allocated. Reasons for cross-over will be explored. Distribution of all variables will be tested by the Shapiro-Wilk test. For the normally distributed variables, parametric tests will be used. For the variables that were not normally distributed non-parametric tests will be used.

The primary outcome will be analyzed by using logistic regression analyses (patient satisfaction with the 12 months’ results of TKA as dependent and intervention as independent variable), variables of which a priori are known to be associated with patient satisfaction, based on previous studies or based on a strong clinical rationale, will be considered as covariates in the primary analysis. These covariates are age, gender, BMI and baseline expectations as assessed by the HSS Knee Replacement Survey, anxiety, depression. The assumptions of constant variance and linear relationships will be assessed using scatter plots. Should any of these assumptions seriously fail, then transformation of the dependent or independent variable(s) (where applicable) will be used. The choice of which transformation (e.g., square root, logarithm) will be used based on the specific distribution of the residuals. Similar analyses will be performed for the secondary outcome parameters. Change in outcome expectations before and after pre-operative education (baseline vs pre-operative), and difference between intervention and control group in change in baseline and pre-operative expectations will be analyzed using linear regression analyses. Statistical calculations will be made using IBM® SPPS software, version 19.0.

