### Setting

The study will be conducted at the Department of Orthopedic Surgery and Trauma of the Máxima Medical Center. This is a large, non-academic teaching hospital where approximately 350 primary TKAs are performed annually. In total, five experienced orthopedic surgeons perform these procedures.

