### Randomization

The randomization procedure will be performed after the patient is cleared for surgery in pre-operative screening by the anesthesiologist, and a definitive date for surgery has been determined. Allocation to type of intervention takes place by receiving the consecutive randomization number from the coordinating investigator. A computer-generated randomization list will be used (Research Manager version 5.30.0.6, Cloud9 Software, Deventer, The Netherlands). Patients will be included by each of the five orthopedic surgeons performing and indicating patients for TKA. Because information on outcome after TKA provided by each orthopedic surgeon during the consultation might be different on details, block randomization with variable size of blocks, stratified for orthopedic surgeon is used. This accounts for potential information bias in this regard. All clinical and trial staff will be blinded for allocation during the study procedure. Patients were invited for a specific education class by mail to avoid cross-over, and only the secretary sending the invitation letters for the education sessions is unblinded. Attendance of the education class in the intervention and control arms is recorded blinded using the data management software. Data analysis will be obtained and analyzed blinded for group allocation. Only after data analysis will unblinding take place.

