#### Primary outcome measure

The primary outcome measure is a Numeric Rating Scale (NRS) score for satisfaction with treatment result at 12 months’ follow-up. The NRS satisfaction score is a self-reported measure for patient satisfaction [45]. Patients are asked to answer the question: “How satisfied are you (in general) about the result of your knee operation?” on a scale ranging from 0 (very dissatisfied) to 10 (very satisfied) [45]. “Very satisfied with treatment result” is defined as an NRS satisfaction score of ≥ 8.

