### Sample size and power calculations

The calculation of the number of patients needed for this trial was based on the following assumptions. Specific pre-operative information can lead to more realistic patient expectations, which subsequently leads to a higher probability of fulfilled expectations [15]. Furthermore, patients who have fulfilled expectations are more often satisfied with the results of TKA [13, 14]. Therefore, we hypothesize that patients are more often (very) satisfied with treatment outcome 1 year post-operative. Based on more realistic expectations after improved pre-operative education on long-term recovery, previous work has shown that 50% of patients are very satisfied after TKA, 23% somewhat satisfied, 11% neutral, 9% somewhat dissatisfied, and 7% were very dissatisfied with the outcome [62]. In our calculation, we used a power of 80% (type II error of 20%) and an alpha of 0.05 (type I error). To increase the proportion of very satisfied patients in the knee population with 20% (from 50% of very satisfied patients to 70% very satisfied patients), 90 patients are required in each group (180 TKA patients in total). The final total sample size required is 204 knee patients, to accommodate a 15% potential dropout rate.

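### Randomisation is stratified by surgeon but the primary model's covariate list omits surgeon: a minor design–analysis mismatch that may forgo a little power and is free to correct

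*Protocol article*

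**What the plan says.** Protocol article, Randomization: "block randomization with variable size of blocks, stratified for orthopedic surgeon is used". The reason given is that "information on outcome after TKA provided by each orthopedic surgeon during the consultation might be different on details", and the section says that stratifying deals with possible information bias of this kind. Setting gives the number of strata: "In total, five experienced orthopedic surgeons perform these procedures".

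Protocol article, Statistical analysis: "The primary outcome will be analyzed by using logistic regression analyses", with 12-month satisfaction as dependent and intervention as independent variable. Covariates are those known beforehand to relate to satisfaction or supported by a strong clinical rationale, and the section names them: "These covariates are age, gender, BMI and baseline expectations as assessed by the HSS Knee Replacement Survey, anxiety, depression". Secondary outcomes are to be handled in a similar way, and missing data by multiple imputation.

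Surgeon does not appear in the analysis section as a covariate, a random effect or the stratum of a stratified test.

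**The concern.** Stratified blocks hold the two arms nearly equal within each surgeon. The treatment comparison is then free of chance imbalance between surgeons. A model without surgeon computes its standard error as if that imbalance could still occur. If surgeons differ in their patients' satisfaction, the reported standard error is too large for the estimator it accompanies, and the test rejects less often than its nominal level.

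At stake is precision, not validity. The sample size has no reserve to absorb even a small loss, and the data needed to avoid it already exist. This is also not a detail left to a later analysis plan, because the article itself names the covariates.

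**Working it through.** **Inputs from the protocol article.** "we used a power of 80% (type II error of 20%) and an alpha of 0.05 (type I error"; rates "from 50% of very satisfied patients to 70% very satisfied patients"; the binary endpoint "is defined as an NRS satisfaction score of ≥ 8"; 1:1 allocation; 90 per group, 180 in total; five surgeons.

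**Assumptions, because the article is silent.** Two-sided alpha; 36 evaluable patients per surgeon; blocks of 2, 4 and 6; surgeon effects evenly spaced on the log-odds scale with the SD shown.

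**1. The plan's own figure.** n per group = (1.960 + 0.842)² × (0.5×0.5 + 0.7×0.3) / 0.20² = 7.849 × 0.46 / 0.04 = 90.26. This reproduces the stated 90. With the pooled variance the requirement is 93, and 90 per group gives 78.7% power.

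**2. Standard error when surgeon is left out (no treatment effect, overall rate 50%).** The model without surgeon reports SE = √[4/(180 × 0.25)] = 0.298. Under stratified allocation only the within-surgeon variance contributes, so the true SD is about 0.298 × √[mean p(1−p) / 0.25], where p is each surgeon's rate. The actual type I error is 2 × [1 − Φ(1.96 / ratio)].

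| Surgeon SD | Rates across surgeons | Mean p(1−p) | Ratio | True SD | Actual type I error |
|---|---|---|---|---|---|
| 0 | 50% | 0.250 | 1.000 | 0.298 | 5.0% |
| 0.3 | 40–60% | 0.245 | 0.989 | 0.295 | 4.8% |
| 0.5 | 33–67% | 0.235 | 0.970 | 0.289 | 4.3% |
| 0.8 | 24–76% | 0.216 | 0.930 | 0.277 | 3.5% |
| 1.0 | 20–80% | 0.201 | 0.898 | 0.268 | 2.9% |

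Simulation agrees: mean model SE 0.300 against an empirical SD of 0.290 at SD 0.5, and 0.300 against 0.270 at SD 1.0.

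**3. Simulated power, treatment and surgeon only.** 4,000 trials per row, overall rates held at 50% versus 70%.

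| Surgeon SD | Type I error without / with surgeon | Power without / with surgeon | Difference (points) |
|---|---|---|---|
| 0 | 4.3% / 5.0% | 79.1% / 80.0% | 0.9 |
| 0.25 | 4.5% / 5.1% | 79.3% / 80.6% | 1.3 |
| 0.5 | 3.8% / 5.1% | 79.1% / 81.5% | 2.4 |
| 1.0 | 2.7% / 5.1% | 80.7% / 86.7% | 6.0 |

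The 0.9 points at SD 0 are not efficiency. They go with the slightly higher rejection rate under the null, and a similar part of the other differences should be discounted.

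**4. Simulated power with baseline expectations also in the model.** Same settings, assuming 0.8 log-odds per SD of expectations. Columns show how much of the surgeon effect runs through expectations; cells show power without / with surgeon.

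| Surgeon SD | None | Half | All |
|---|---|---|---|
| 0.5 | 84.6% / 85.8% | 85.2% / 85.8% | 84.7% / 84.8% |
| 0.8 | 82.3% / 86.0% | 86.2% / 87.4% | 86.4% / 86.8% |

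At SD 0 the figures are 83.0% / 83.7%. At SD 0.3 the difference is 0.6–0.9 points. Type I error without surgeon is 4.2–5.3% up to SD 0.5. At SD 0.8 it is 3.6%, 4.4% and 5.0% for none, half and all. The Monte Carlo standard error near 5% is √(0.05 × 0.95 / 4,000) = 0.3 points, so 5.3% is not evidence of inflation.

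**The case against.** The strongest objection is that the one route the protocol names is largely covered already. The worry in the Randomization section is what the surgeon tells the patient in the consultation. Under Recruitment, consent and baseline measurement follow that consultation, so baseline expectations are recorded after the surgeon has spoken, and they are in the model. If the whole surgeon effect runs through expectations, adding surgeon gains at most 0.4 points in step 4. This stands and limits the size of the point. It does not cover surgeon differences by other routes, such as operative technique.

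A reader might infer that the sponsor expects surgeons to affect satisfaction. The text says only that information might differ in detail and calls the bias potential; it states no effect on the outcome.

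A reader might also infer that power drops far below 80%. Holding the odds ratio at (0.7/0.3)/(0.5/0.5) = 2.33 within surgeon, simulated power at SD 0.8 is 66.9% without surgeon and 71.9% with it. Most of that shortfall is not the cost of omitting surgeon. A fixed within-surgeon odds ratio shrinks the overall intervention rate to 67.6%. By the formula in step 1, power with 90 per group then falls from Φ(0.200/√(0.46/90) − 1.96) = 80% to Φ(0.176/√(0.469/90) − 1.96) = 69%, before any question of adjustment. At the protocol's own overall rates, power without surgeon stays at 79.1–80.7% in step 3.

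**Conclusion.** The mismatch is real: the only stratification factor is absent from a covariate list that the article itself fixes. Its consequence is conditional and small. If surgeon predicts satisfaction beyond the listed covariates, the test is slightly conservative and about 1–2 points of power are forgone at an assumed SD of 0.3–0.5, or about 3–4 points at SD 0.8 when the effect bypasses expectations. If surgeon is not prognostic, nothing is lost.

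The size rests on assumed surgeon effects, equal surgeon volumes and an assumed weight for expectations. Age, gender, BMI, anxiety and depression were not simulated.

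The documents do not support a claim that the primary test is invalid: any error is towards too few rejections. Nor does stratification fail without adjustment, because the arms remain balanced by surgeon. What is forgone is the precision that this balance could bring. This is a minor point.

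**What to change.** Add orthopedic surgeon as a fixed covariate with five levels (four indicator terms) to the primary logistic model and to the secondary between-group models, including the regression on change in expectations. Include surgeon in the multiple-imputation model so that imputation and analysis agree. State this before unblinding; the Randomization section places unblinding after the analysis, so the change can be fixed without knowledge of results by group.

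The cost is one sentence of analysis text and four degrees of freedom. Surgeon is already known for every patient from randomisation, and no new data or patients are needed. The treatment odds ratio then becomes conditional on surgeon as well as on the covariates already listed, and the report should say so.

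### Linear-model checks and outcome transformation are written for the logistic primary model, and a normality pre-test conflicts with the adjusted regressions planned for secondary outcomes

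*Protocol article*

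**What the plan says.** All the rules at issue stand in the Statistical analysis section of the protocol article.

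- **General paragraph.** "Distribution of all variables will be tested by the Shapiro-Wilk test". Normal variables get parametric tests; for the rest, "For the variables that were not normally distributed non-parametric tests will be used".
- **Primary model.** "The primary outcome will be analyzed by using logistic regression analyses", with intervention as the independent variable. "These covariates are age, gender, BMI and baseline expectations as assessed by the HSS Knee Replacement Survey, anxiety, depression".
- **Checks, directly after the covariate list.** "The assumptions of constant variance and linear relationships will be assessed using scatter plots". Then: "Should any of these assumptions seriously fail, then transformation of the dependent or independent variable(s) (where applicable) will be used". The type of transformation, with square root and logarithm as examples, is to be picked from how the residuals are distributed.
- **Secondary outcomes, after the checks.** Secondary parameters are to be analysed in the same manner as the primary outcome, and change in expectations by linear regression.

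The Primary outcome measure section says: "The primary outcome measure is a Numeric Rating Scale (NRS) score for satisfaction with treatment result". Being very satisfied "is defined as an NRS satisfaction score of ≥ 8". The sample size is built on the proportion in that category. The dependent variable of the logistic model is therefore taken here to be NRS ≥ 8, yes or no, although the analysis section does not say so outright.

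**The concern.** There are two separate problems.

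First, because of where they stand, the variance check and the outcome transformation attach to the primary logistic model. They belong to linear regression. An analyst following the text would check something the model does not assume. The assumption the model does make about its continuous covariates would be checked with an unsuitable plot.

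Second, for a secondary score that fails the normality test, the section gives two instructions that lead to different analyses, and it does not say which prevails. The choice of test, the scale of the effect and whether the named covariates are used would then depend on the observed data. Readers of the results could not tell which analysis had been planned.

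**Working it through.** The plan attaches no figure to this point, so there is none to reproduce. The check is mainly one of logic.

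**1. Constant variance in the primary model.** Inputs: 50% and 70% very satisfied (Sample size and power calculations). The variance of a 0/1 outcome is p(1-p).
- At 50%: 0.50 × 0.50 = 0.25.
- At 70%: 0.70 × 0.30 = 0.21.

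The variance follows from the mean by construction. Logistic regression builds this in and makes no constant-variance assumption.

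**2. Transforming the primary outcome.**
- Square root: 0 stays 0 and 1 stays 1.
- Logarithm: log(0) is undefined; log(y+1) gives 0 and 0.693, which is still two values.

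A transformation of a two-valued outcome therefore changes nothing or fails. If an ordinal logistic model of the 0-10 score were meant instead, an increasing transformation would leave the ordering, and so the model, unchanged.

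**3. What does apply.** Of the listed covariates, age, BMI, HSS expectations, anxiety and depression are continuous or scores. Each is assumed to act linearly on the logit unless another form is chosen. A plot of 0s and 1s against a covariate gives two horizontal bands and says little about the shape on the logit. Transforming a covariate is a legitimate remedy, but here its choice is left to the observed residuals.

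**4. Secondary outcomes: the rules side by side.** Take any score listed under Secondary outcome measures that fails Shapiro-Wilk, for example KOOS-PS (0 to 100).

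| Rule followed | Analysis | Effect reported | Named covariates |
|---|---|---|---|
| Same manner as the primary outcome, or linear regression | Regression, original scale | Adjusted mean difference | Used |
| Transformation rule | Regression, square-root or log scale | Difference on another scale | Used |
| Shapiro-Wilk rule | Non-parametric test | Rank comparison | None mentioned |

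These are three different analyses, with no order of precedence. The pre-test also answers a different question: linear regression does not require the outcome or the covariates to be marginally normal.

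**5. How readily the pre-test would reject (illustration only).** The protocol gives no score distributions. As an assumption, an 11-point score was simulated as a normal variable with SD 2, rounded and limited to 0-10, with 2,000 data sets per setting, tested at 5%.

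| Assumed mean | n = 90 | n = 180 |
|---|---|---|
| 7, 7.5 or 8 | 100% rejected | 100% rejected |
| 5 | 82% rejected | 100% rejected |

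Under these assumptions a coarse 0-10 score such as NRS pain would usually trigger the rule. The simulation says nothing about the longer questionnaire scores.

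**The case against.** Five points can be made in favour of the plan.

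- **Shapiro-Wilk does not choose the primary analysis.** This stands. A reader might infer that it does, but the rule is in a general paragraph about tests, and the next paragraph fixes logistic regression without condition.
- **Not every check is out of place.** This stands. A reader might infer that the whole set of rules is inapplicable. Linearity of covariates, and transformation of independent variables to achieve it, are proper concerns in logistic regression.
- **The words in brackets in the transformation sentence allow it to be skipped for a binary outcome.** This stands in part. It means the primary analysis is not blocked. It does not rescue the constant-variance check or improve the check of linearity.
- **The specific sentences on regression should override the general one on tests, which may be meant only for simple comparisons and descriptives.** This is a possible reading, so the document does not support saying that adjusted models will nearly always be abandoned. But the rule is worded for all variables and no precedence is stated, so the conflict remains. Nor is it true that no rank-based method can adjust for covariates; the plan simply names none.
- **The Randomization section has the data analysed before unblinding.** This makes it harder to steer a choice towards one arm. It does not fix the test, scale or adjustment in advance.

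**Conclusion.** The point holds in two limited parts. The constant-variance check and the residual-based transformation of the outcome are misplaced on the primary logistic model, and the one relevant check, linearity on the logit, is poorly served by a scatter plot. For continuous secondary outcomes, the normality rule conflicts with the adjusted regressions in the same section and makes the analysis depend on the data.

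A reader might go further and infer that the primary result is at risk. The document does not support that: the model is named without condition, and its covariates are listed.

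The size for secondary outcomes cannot be computed. The protocol gives neither score distributions nor correlations between covariates and outcomes. It also does not list each outcome's own baseline as a covariate, so no such adjustment can be said to be lost. The conclusion rests on reading the dependent variable as NRS ≥ 8, and on reading the sentence about secondary outcomes as promising regression with covariates. It is worth correcting, but it does not undermine the trial.

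**What to change.** Four changes to the Statistical analysis section:

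1. Confine the constant-variance check to the linear regressions.
2. For the logistic model, name NRS ≥ 8 as the dependent variable and fix the form of the continuous covariates in advance, for example linear on the logit.
3. Delete Shapiro-Wilk as a means of selecting the test.
4. Analyse continuous secondary outcomes by covariate-adjusted linear regression on the original scale whatever the normality result, with robust or bootstrap standard errors. Keep any transformed-outcome or rank analysis as a sensitivity analysis.

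The cost is a few rewritten sentences, settled before unblinding. No new data and no extra patients are needed.

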**Methods:**

The EKSPECT study is a randomized controlled trial. Patients with symptomatic and radiographic knee osteoarthritis who are indicated for a primary TKA will be randomized to the usual pre-operative education (control group) or usual education plus an additional module on realistic expectations for long-term recovery (intervention group). Patients will be naïve to study objective and difference between study groups. Outcome expectations will be measured blinded for group allocation using the HSS Knee Replacement Expectations Survey at baseline (before the intervention), pre-operatively (after the intervention) and fulfillment of expectations at 12-month follow-up. Baseline physical function, quality of life and psychological factors are measured using self-reported questionnaires. The primary outcome measure is satisfaction with treatment result at the 12-month follow-up.

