#### Secondary outcome measures

##### Hospital for Special Surgery (HSS) Knee Replacement Expectations Survey

Patient expectations will be evaluated by the Dutch version of the HSS Knee Replacement Survey [34]. Measurements will be obtained at baseline (after inclusion at the outpatient clinic, before pre-operative education), at admission for surgery (after the pre-operative education) and fulfillment of expectations 12 months post-operatively. The HSS Knee Replacement Expectations Survey is a 19-item, self-administered survey, measuring probability-based outcome expectations in the domains of pain, function, activities and psychological wellbeing [7, 15]. The survey is reliable, validated, and considered to be a high-quality expectation assessment instrument [7, 34, 47]. Patients will be asked how much improvement they expect for each item; the following response format will be used: “complete improvement or back to normal,” “a lot of improvement,” “a moderate amount of improvement,” “a little improvement” or “this expectation does not apply to me/I do not have this expectation” [15, 34]. The total score ranges from 0 to 76, which will be recoded on a 100-point scale, with a higher score representing higher expectations [15, 34].

To assess to what extent expectations have been fulfilled 12 months post-operatively, the expectation fulfillment version of the HSS Knee Replacement Expectations Survey will be used [12]. Unfortunately no evaluation of the measurement properties of this modification are available. The perceived actual outcome is scored with the same answer options and score calculation as used for pre-operative measurement [12].

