##### Anchor question

At the follow-up 12 months post-operative a 7-point Likert scale anchor question will be scored for change in activities of daily living. The question “How has your general daily functioning changed since the operation on your knee?” can be responded to on a 7-point scale ranging from 1 (a lot worse) to 7 (very much improved).

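### The one covariate list was chosen for satisfaction and holds no baseline function or quality-of-life score, so KOOS-PS, OKS and EQ-5D comparisons, as written, forgo a free gain in precision

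*Protocol article*

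**What the plan says.** The Statistical analysis section describes a logistic model for satisfaction at 12 months. It selects covariates as "variables of which a priori are known to be associated with patient satisfaction", from earlier studies or on clinical grounds, and then names them: "These covariates are age, gender, BMI and baseline expectations as assessed by the HSS Knee Replacement Survey, anxiety, depression". The other outcomes get one sentence: "Similar analyses will be performed for the secondary outcome parameters". Expectations before surgery have their own rule: the "difference between intervention and control group in change in baseline and pre-operative expectations will be analyzed using linear regression analyses".

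On what is available at baseline, the abstract states: "Baseline physical function, quality of life and psychological factors are measured using self-reported questionnaires". The HSS section states: "Measurements will be obtained at baseline (after inclusion at the outpatient clinic, before pre-operative education", with later measurements at admission and at 12 months. Under Recruitment and Randomization, baseline measurements are registered at consent, and randomisation follows only after pre-operative clearance. Baseline scores are therefore pre-randomisation covariates.

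The Intervention arm section names pain severity and functional status before surgery among the factors that modify an individual patient's outcome.

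**The concern.** Satisfaction with the result of an operation has no baseline value, so a covariate list built for it naturally contains none. KOOS-PS, OKS and EQ-5D differ: the same construct is scored before and after surgery, and the earlier score is often among the best predictors of the later one. The protocol itself treats functional status before surgery as a predictor of outcome, yet the only list it offers has no function, pain or quality-of-life score in it.

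Two things are at stake for these secondary comparisons. The standard errors would be larger than the collected data require. Also, if the arms happen to differ at baseline, part of that difference would pass into the 12-month estimate. The trial was sized on satisfaction alone, so precision for the secondary scores depends on how they are analysed. Deciding on baseline adjustment after an imbalance has been seen would be data-driven, which is a reason to state it beforehand.

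The expectations analysis raises a smaller question. It compares change between the arms, and the sentence does not say whether baseline HSS is also in that model.

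**Working it through.** **Which outcomes are concerned**

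- KOOS-PS, OKS, EQ-5D: measured at baseline according to the abstract (physical function, quality of life); own baseline not in the list.
- NRS pain: not in the list. Its section gives no time points and the schedule figure is not shown, so a baseline is likely but unconfirmed.
- HSS expectations, anxiety, depression: own baseline already in the list.
- Anchor question: "At the follow-up 12 months post-operative a 7-point Likert scale anchor question will be scored for change in activities of daily living". There is no baseline to add.
- Complications: scored at 1 year. There is no baseline to add.

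**Number per arm**

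The Sample size section gives 50% against 70% very satisfied, and "we used a power of 80% (type II error of 20%) and an alpha of 0.05 (type I error". Sidedness is not stated; I take two-sided. With unpooled variance:

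n = (0.50×0.50 + 0.70×0.30) × (1.960 + 0.842)² / 0.20² = 0.46 × 7.85 / 0.04 ≈ 90.3 per group.

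This reproduces the stated 90, which I use below. The plan gives no figure for the secondary outcomes.

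**Precision**

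Let r be the partial correlation between the 12-month score and its own baseline, given the listed covariates. The documents do not give r, so the values below are assumptions. Let SD be the residual SD under the listed covariates alone.

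- Residual variance after adding the baseline: multiplied by 1 − r².
- Standard error: multiplied by √(1 − r²).
- Equivalent increase in patients: 1/(1 − r²).
- Detectable difference without the baseline, 80% power, two-sided 0.05: (1.960 + 0.842) × √(2/90) = 2.802 × 0.149 = 0.418 SD. With the baseline: 0.418 × √(1 − r²).

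| Assumed r | Variance factor | SE factor | Patient equivalent | Detectable difference (SD) | Power at 0.418 SD |
|---|---|---|---|---|---|
| 0.2 | 0.96 | 0.980 | 1.04 | 0.409 | 81.6% |
| 0.3 | 0.91 | 0.954 | 1.10 | 0.398 | 83.6% |
| 0.4 | 0.84 | 0.917 | 1.19 | 0.383 | 86.4% |
| 0.5 | 0.75 | 0.866 | 1.33 | 0.362 | 89.9% |
| 0.7 | 0.51 | 0.714 | 1.96 | 0.298 | 97.5% |

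**Chance imbalance**

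The baseline difference between arms has SE √(2/90) = 0.149 SD. The part carried into an estimate that ignores the baseline is r times the imbalance:

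- 1 SE: 0.3 × 0.149 = 0.045 SD, up to 0.5 × 0.149 = 0.075 SD.
- 1.96 SE (0.292 SD): 0.088 SD at r = 0.3 and 0.146 SD at r = 0.5.

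**Expectations**

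Write the change model with baseline as a covariate:

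Y1 − Y0 = a + τ·arm + b·Y0 + … is the same as Y1 = a + τ·arm + (b + 1)·Y0 + …

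The treatment effect τ, its residuals and its SE are identical to those from ANCOVA of the admission score. Only if baseline HSS is absent does the choice matter. With equal variances, the variance of the raw-change comparison relative to ANCOVA is 2(1 − r)/(1 − r²) = 2/(1 + r), where r is now the simple correlation between baseline and admission HSS. At an assumed 0.5 this is 2/1.5 = 1.33.

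**The case against.** The best reply is that the article does not say the same list is reused. The covariates are attached to the primary analysis, and the word similar cannot mean identical, since the primary model is logistic and these scores are not binary. Applied to OKS or KOOS-PS, the stated principle (known predictors of the outcome) would bring in the baseline score. A condensed article may also leave outcome-specific covariates to the full plan. This stands as far as intent goes: reuse is an inference. But the article chose to name its covariates and to extend the method in one sentence. The only list a reader can apply has no such score.

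Other points that stand:

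- A reader might infer that every secondary outcome lacks its own baseline. That is not so: HSS expectations, anxiety and depression are listed, and the anchor question and complications have none.
- A reader might infer bias. Randomisation keeps the estimates unbiased, and their confidence intervals already allow for chance imbalance. The loss is one of precision.
- The relevant quantity is the partial correlation. It may be smaller than the simple one, because the listed covariates may already explain part of the baseline score. At 0.3 or below the gain is small.
- Between-group effects on function, pain and quality of life are not among the objectives in the Trial objectives section.
- A reader might infer that analysing change in expectations is wrong. If baseline HSS is in that regression, it gives exactly the ANCOVA treatment effect.

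**Conclusion.** The point holds for KOOS-PS, OKS and EQ-5D, and for NRS pain if it is measured at baseline. As written, their 12-month comparisons do not use their own baseline values. Under an assumed partial correlation of 0.3 to 0.5, adjustment would reduce residual variance by 9 to 25% and the standard error by about 5 to 13%, equal to having 10 to 33% more patients. The result rests on that assumed correlation, on 90 evaluable patients per arm, and on reading the sentence about secondary outcomes as carrying the named list over unchanged.

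For HSS expectations there is an ambiguity to settle, not a demonstrated error. Nothing here touches the primary outcome, which has no baseline, or the sample size. It is a free improvement to the secondary analyses, not a threat to the trial's main conclusion.

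**What to change.** In the Statistical analysis section, replace the sentence on secondary outcomes with a statement to this effect: each continuous secondary outcome that is also measured at baseline will be analysed by a linear model of the 12-month score on arm, the baseline value of that same score, the listed covariates and surgeon. Surgeon belongs there because randomisation is stratified by it; with five surgeons it uses four parameters. Name the outcomes covered (KOOS-PS, OKS, EQ-5D and, once the schedule confirms a baseline, NRS pain).

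For expectations, add that baseline HSS is a covariate in the regression of change from baseline to admission.

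The cost is a few lines of wording, fixed before unblinding. Baseline function and quality-of-life scores are already collected, so no new measurement, visit or patient is needed.
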